**ASSESSMENTS:**						
Sociodemographic data		X		X		
Clinical data		X		X	X	X
VAS						X

Legend:

P1: moment immediately before arterial sheath removal (30 min before)

P2: moment during arterial sheath removal

F1: moment after arterial sheath removal (15 min later)

*VAS *Visual Analog Scale

Patients participating in the study will be monitored throughout their stay in the hemodynamic admission/recovery room. In this sense, after carrying out the cardiac catheterization and returning to the aforementioned room, the patient will be approached in an attempt to recruit and select the sample. After applying the inclusion and exclusion criteria, patients will be asked to sign the informed consent form, guaranteeing their participation in the study and allocation to control or experimental groups. At this initial moment, sociodemographic data and the first part of clinical data will already be completed, initiating their follow-up.

After the initial 30 min, if the patient's blood pressure is within acceptable limits, the health professional will remove the arterial sheath via the femoral route. At this point, the second part of the instrument referring to clinical data will be completed, continuing the follow-up.

Finally, after arterial sheath removal and after 15 min of arterial compression according to the service protocol, the headphones will be removed and the third and last part of the instrument referring to clinical data will be completed and finished with the VAS application for the identification the pain intensity. After performing the compressive dressing, the individual will spend four hours keeping the limb at rest until discharged from the unit, at which time follow-up will be completed.

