### Follow-up

Table 1 describes the adapted SPIRIT schedule with appropriate enrollment times, interventions and participant assessments.

**Table 1 Tab1:** Standard protocol items: adapted recommendations for interventional trials (SPIRIT) schedule: enrollment, interventions and evaluations

STUDY PERIOD						
	**Enrolment**	**Baseline**	**Post-allocation: Allocation, Interventions, Follow-up**			
**TIMEPOINT**			**Allocation**	**P1**	**P2**	**Follow-up (F1)**

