#### Blinding

The study will have the participation and involvement of two researchers. Researcher 1 (R1) will be responsible for the recruitment and initial selection of individuals that will compose the sample, as well as for guaranteeing their participation by signing the Free and Informed Consent Form (FICF), performing the randomization and allocation of patients and application of headphones in both groups. The second researcher will be responsible for applying the data collection instruments during the intervention and at the end of the painful procedure. Thus, the second researcher, service health professionals and patients will not know to which groups patients will be allocated.

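### Allocation is placed before the P1 readings and before the blood-pressure condition for sheath removal, although nothing differs between groups until P2, and P1 is not assigned to the blinded researcher

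*Protocol article*

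**What the plan says.** **Order of steps.** The columns of Table 1 (Follow-up section) run Enrolment, Baseline, Allocation, P1, P2, F1, and P1 sits under the heading "Post-allocation: Allocation, Interventions, Follow-up". The legend defines "P1: moment immediately before arterial sheath removal (30 min before"). The text below the table has patients sign consent, "guaranteeing their participation in the study and allocation to control or experimental groups", and continues: "At this initial moment, sociodemographic data and the first part of clinical data will already be completed". After the first 30 minutes comes the condition: if the patient's "blood pressure is within acceptable limits, the health professional will remove the arterial sheath via the femoral route".

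**When the groups start to differ.** Table 1 marks headphones, with or without music, at P2 and F1 only.

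**Who does what.** The Blinding section gives R1 recruitment, consent, "performing the randomization and allocation of patients and application of headphones in both groups". For the other researcher it says: "The second researcher will be responsible for applying the data collection instruments during the intervention and at the end of the painful procedure". The second researcher, the service's professionals and the patients are listed as unaware of the group. R1 is not on that list.

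**What is measured.** The Questionnaire section collects vital signs, oxygen saturation and observed signs of pain before, during and 15 minutes after the procedure. The Primary outcome section counts reductions in blood pressure, heart rate and respiratory rate, and improved saturation, alongside the VAS. Table 1 schedules the VAS at F1 alone.

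**The concern.** A pre-procedure reading is a clean reference only if it is taken before the group is known, or by someone who does not know it. Here the schedule puts P1 after allocation, and the division of labour leaves P1 outside the blinded researcher's task. If R1 takes P1 and the second researcher takes P2 and F1, the rater and the state of blinding both change between the reference and the outcome. Respiratory rate, pallor and facial expression leave the most room for judgement.

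Randomising before a waiting period and a condition for proceeding also means that a patient can be counted as randomised and then never reach the point where the groups differ. That is an avoidable post-randomisation loss, and the article states no path for such a patient.

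**Working it through.** The documents give no figure to reproduce on this point, so the check sets the passages side by side.

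1. **Does allocation precede P1?** In Table 1, yes, by column order. In the Follow-up text, consent, allocation and the first part of the clinical data all belong to one initial phase, followed by about 30 minutes of waiting. P1 is defined as 30 minutes before removal, so it falls at the start of that wait. The text does not say whether the first clinical data come before or after allocation within that phase; it merely mentions allocation first.

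2. **How many assessments are there?** The Abstract, the Questionnaire section and the Discussion give three moments: before, during and 15 minutes after. The Follow-up text describes three parts of the clinical instrument. Table 1 marks clinical data in four columns (Baseline, P1, P2, F1) and sociodemographic data in two (Baseline and P1). Two readings are possible:
   - The first part is the Baseline column. It then precedes allocation, and the P1 marks are surplus or a repeat.
   - The first part is P1, as the legend's definition suggests. It then follows allocation.

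   The article does not settle which holds.

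3. **Does allocation precede the blood-pressure condition?** Yes, in both table and text. The condition is applied after the 30 minutes; allocation belongs to the phase before them.

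4. **Is early allocation needed?** No. Headphones begin at P2 in both groups, so nothing between consent and P2 depends on the group.

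5. **Who takes P1?** The Blinding section says two researchers are involved and limits the second to the during and end assessments. Data management says both are trained to collect data. The Questionnaire section gives the initial form to the principal researcher, who is not identified as R1 or R2, and does not name who measures the vital signs. By elimination R1 is the likely P1 assessor, but no sentence says so.

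6. **Which outcomes are exposed?** Only the vital signs, saturation and observed pain signs. The VAS has no P1 value in Table 1.

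7. **Who would be lost?** P2 is defined as during removal and F1 as 15 minutes later, so both move with the removal. A delayed patient still has both. A loss needs an allocated patient who never proceeds, or one who withdraws during the wait. For scale, each such patient is 1/68 = 1.5% of the planned sample, or 1/34 = 2.9% of one group. How many there would be cannot be derived from the documents.

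**The case against.** The strongest reply is that a reading before allocation appears to be planned already, since Table 1 marks clinical data at Baseline. No passage says that vital signs are analysed as change from P1 rather than from Baseline or between groups. The blood-pressure condition applies before any music is heard, and the service's professionals are listed as blinded, so patients held back by it should be unrelated to group. Much of this stands. It limits the likely bias, and it makes the order of Baseline, Allocation and P1 something to reconcile, not a proven error.

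Several stronger readings are tempting, and the documents do not support them:

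- *R1 certainly takes P1 unblinded.* This is an inference by elimination. What the text shows is that P1 is not assigned to the blinded researcher.
- *The pain score is biased through P1.* With the VAS scheduled only at F1, a P1 assessor cannot distort it.
- *A delayed removal leaves no usable P2 or F1.* Both are timed from the removal itself.
- *Patients not meeting the blood-pressure condition are replaced.* The rule in Data management covers those who withdraw. Waiting for blood pressure to settle is not withdrawal, and nothing says that removal is then cancelled.

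The reply does not show any benefit from allocating early, and it does not name a blinded assessor for P1.

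**Conclusion.** The point holds as a modest, inexpensive improvement. As scheduled, allocation comes before P1 and before the condition for removal, with no operational reason for it, and the P1 vital signs and pain signs are not assigned to a blinded assessor. The article also leaves unclear whether Baseline and P1 are one assessment or two.

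The size cannot be stated. The direction and amount of any assessor bias are unknown, and they matter only if P1 serves as the reference in the analysis. The weight also depends on where the vital signs rank: the Primary outcome section includes them, while the Abstract lists them as secondary. That conflict is a separate matter.

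Post-randomisation loss is possible but unquantified. It is confined to allocated patients who never proceed or who withdraw while waiting. For the latter, the replacement rule places the next eligible participant in the same group, so that participant's group is fixed in advance and not randomised. This gives a further reason to shorten the interval between allocation and removal.

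**What to change.** - Move the Allocation column in Table 1 to after P1, and reorder the Follow-up text to match: consent, forms, P1 readings, then allocation.
- State whether Baseline and P1 are the same assessment. If they are, keep one column. If not, say what is recorded at each and by whom.
- In the Blinding section, give the P1 readings to the second researcher, who is still blind at that time.
- Have R1 reveal the next concealed allocation and fit the headphones only when staff confirm that removal will proceed.
- State how an allocated patient who nevertheless does not proceed is counted.

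The clinical blood-pressure rule is unchanged, and no visit or measurement is added. The cost is a reordering of Table 1 and a few sentences, plus the second researcher's presence at P1. The practical downside is that revealing the allocation and fitting the headphones must fit into the few minutes before removal, so the randomisation result has to be ready at the bedside without being visible beforehand.

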**Methods:**

This is a randomized controlled clinical trial, with two arms and a single-blind design to be carried out with 68 patients equally allocated into control and experimental groups. The intervention will be applied with the use of headphones without any musical transmission in the control group or with the patient’s musical preference in the experimental group with sound intensity of 60 dB. These patients will be evaluated in three moments: immediately before, during and 15 min after the painful procedure. The primary outcome includes reduction of pain intensity verified by the Visual Analogue Scale and the secondary outcome corresponds to improvement of vital signs and vocal and facial pain expressions.

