### Objective

To evaluate the effectiveness of music therapy to relieve pain in adults and older adults during femoral arterial sheath removal after cardiac catheterization.

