#### Questionnaire

At first, the principal researcher will apply a form previously prepared with participants of both groups containing the following sociodemographic data: date of birth, age, sex, color, marital status, schooling, profession, family income and musical preference.

At this time, the initial part of the second previously prepared form will also be applied, containing the following clinical data: comorbidities, reason for performing cardiac catheterization and medications in use. After completing this part, blood pressure, heart and respiratory rate vital signs will be measured, as well as information regarding oxygen saturation, presence or absence of bodily signs and symptoms of pain such as sweating, pallor, vocal or face expression or pain. These data will be recorded in the second previously prepared form and repeated during the intervention and 15 min after the end of the painful procedure.

This second form also contains information regarding the French number of the arterial sheath, the professional responsible for removing it, if there were complications during the painful procedure and what these complications were; if there were complications after the procedure and what these complications were; how long the arterial compression lasted after the intervention; if there was need for analgesia after the procedure and the time to receive the hemodynamic discharge. Finally, the Visual Analog Pain Scale will be applied to identify pain intensity.

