## Results

### Primary outcome

The primary outcome expected is reduction in pain intensity through the Visual Analogue Scale (VAS) [17] and reduction in the following physiological parameters: blood pressure, heart and respiratory rate, in addition to the improvement of oxygen saturation levels through the application of the patient's musical preference using headphones during the removal of the arterial sheath via the femoral route after cardiac catheterization.

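### The primary VAS is taken once, 15 min after sheath removal, with no stated reference period, so it captures neither self-reported pain during removal nor any within-patient reduction

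*Protocol article*

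**What the plan says.** The Objective section reads: "To evaluate the effectiveness of music therapy to relieve pain in adults and older adults during femoral arterial sheath removal after cardiac catheterization". The Methods part of the abstract states: "The primary outcome includes reduction of pain intensity verified by the Visual Analogue Scale". The Primary outcome section also describes a reduction in VAS pain, attributed to music played while the sheath is removed. It adds blood pressure, heart rate, respiratory rate and oxygen saturation.

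On timing, the abstract says: "These patients will be evaluated in three moments: immediately before, during and 15 min after the painful procedure". Table 1 calls these moments P1 (before removal), P2 (during removal) and F1 (15 min after).

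The VAS itself appears in three places:

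- **Table 1:** one mark, in the F1 column.
- **Follow-up text:** after removal, 15 min of compression and removal of the headphones, "the third and last part of the instrument referring to clinical data will be completed and finished with the VAS application".
- **Questionnaire section:** vital signs, saturation and bodily signs of pain are listed as recorded at the start and then repeated during and after the procedure. The VAS is not in that list. It closes the section: "Finally, the Visual Analog Pain Scale will be applied to identify pain intensity".

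**The concern.** The outcome that decides the trial should be measured at the time, and in the form, that the objective names. Here the objective concerns pain during a short procedure, while the primary scale is first used when the procedure, the compression and the music are all over.

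A result on that scale could be reported as an effect on pain during removal when the rating was of a later state. A null result would be hard to interpret, because it would not show whether music failed during removal or whether the rating came too late to see an effect. The word reduction also invites a before-and-after reading that the data cannot support. A rating not taken at the bedside cannot be recovered at analysis, so this has to be settled before data collection.

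**Working it through.** The check is a comparison of the schedule with the stated aim, since the protocol gives no figure on this point to reproduce.

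**Step 1. What is collected when (Table 1 and its legend).**

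| Item | Baseline | P1 | P2 | F1 |
|---|---|---|---|---|
| Clinical data (vital signs, saturation, observed pain signs) | yes | yes | yes | yes |
| Headphones, either arm | no | no | yes | yes |
| VAS | no | no | no | yes |

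The clinical data row, directly above the VAS row, carries marks at every one of these moments. The table therefore does separate repeated items from the single VAS.

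**Step 2. Is the single mark a slip or a broken table?** The Follow-up text independently puts the VAS at the close of the third part of the form and mentions none in the first or second part. The Questionnaire section leaves it out of the repeated items. That section's order is not strictly chronological, because it names time to discharge before the VAS, although discharge follows four hours of rest. The timing therefore rests on Table 1 and the Follow-up text, and those two agree.

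**Step 3. Can a reduction be computed?** A within-patient reduction is D = VAS(earlier) − VAS(F1). One reading per patient is scheduled and D needs two, so D is undefined.

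**Step 4. What can be estimated?** The between-arm contrast, mean VAS(F1, control) − mean VAS(F1, experimental), is available and is protected by randomisation. It estimates the effect on whatever the F1 rating refers to. The Follow-up text says only that the rating identifies pain intensity. Read as current pain, the contrast concerns pain 15 min after removal. To concern pain during removal, the form would have to ask for recall, and no section says that it does.

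**Step 5. What does a missing baseline cost?** Adjusting for a baseline with correlation r to the outcome multiplies the residual variance by 1 − r². The protocol gives no r. Assuming r from 0.3 to 0.6:

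- r = 0.3: 1 − 0.09 = 0.91, a 9% reduction in variance;
- r = 0.6: 1 − 0.36 = 0.64, a 36% reduction.

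This is forgone precision, not bias. If most patients have little pain before removal, r could lie at or below the low end.

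**Step 6. Analgesia.** Eligibility excludes previous analgesia, and the second form records whether analgesia was needed after the procedure. Neither says whether any dose came before or after the F1 rating, so its bearing on that rating cannot be judged from the form.

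**The case against.** Several points can fairly be made in the protocol's favour.

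- **Pain during removal is recorded.** A reader might infer from the VAS schedule that the trial measures no pain during removal. The documents do not support that. Facial and vocal signs, sweating and pallor are recorded at all three moments, and the Secondary outcome section includes verbal report. This stands, but these are secondary outcomes and mostly observer judgements. They do not replace the patient's own rating on the primary scale. Nor do the vital signs listed under Primary outcome.
- **A post-only comparison of randomised groups is unbiased.** Reduction can be read as lower pain with music than without, and neither statement of the primary outcome says change from baseline. This stands too, so it would go too far to say that the trial cannot yield a valid result. What it yields on the VAS is a valid answer about a later time.
- **The F1 rating may be meant as recall.** Possibly, but the form and text do not say so. The silence is part of the problem.
- **The three-moment statement is not literally false.** The abstract says that patients are evaluated at three moments, and the clinical data satisfy that. It suggests a three-moment VAS without promising one, so it is better treated as misleading for the primary scale than as a direct contradiction.
- **A rating during removal has costs.** Questioning a patient who is wearing headphones could interrupt the music or reveal the allocation to the second researcher, who is meant to be blind. This is a good reason to ask immediately on completion, and the fix takes it up.

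**Conclusion.** The point holds for the primary pain measure. The VAS is scheduled at one of three moments, F1. It has no stated reference period and no reading before or during removal. It therefore does not capture self-reported pain at the time the objective names, and it permits neither a within-patient reduction nor baseline adjustment. The randomised F1 comparison stands, as an estimate for pain 15 min after removal.

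A reader might go further and infer a particular loss of power from pain, or the effect on it, fading by F1. The documents do not support a figure. They give no course of pain over those 15 min, the interval includes arterial compression and is not shown to be free of pain, and the Sample size section ties its effect of 0.50 to no time point. The precision range for a baseline rests on assumed correlations and is illustrative only.

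The conclusion depends on Table 1 and the Follow-up text meaning what they say, and on there being no unstated instruction to rate recalled pain. It should be corrected before recruitment: the mismatch affects the primary outcome and cannot be repaired afterwards.

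**What to change.** Amend Table 1, the Follow-up text and the second form together:

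1. Add a VAS at P1, before the headphones are fitted.
2. Add a VAS immediately on completion of sheath removal, with wording that asks explicitly about pain during removal.
3. Name that second rating as the primary time point, and compare it between arms with adjustment for the P1 rating.
4. Keep the F1 VAS as a secondary outcome, state its reference period, and record the time of any analgesia relative to it.
5. Restate the primary outcome in the abstract and the Primary outcome section to match.

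The rating on completion should be asked identically in both arms, for example with a printed card of fixed wording. The headphones should stay on, and the patient should be asked not to say what is being heard, so that the music is not interrupted and the second researcher stays blind.

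The cost is two extra one-item ratings per patient, or 2 × 68 = 136 in all, at points where the form is already being filled in. It also needs a short training note and an amendment. If recall at F1 was what the investigators intended, the least they must do is say so in the form and the protocol; that would settle the reference period but would still leave no baseline.

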### Sample size

The sample size calculation was performed using the G Power software, version 3.1.9.2, with Cohen effect of 0.50, test power of 0.80 and significance level of 5%, establishing N of 34 patients per group, experimental and control, totaling 68 patients.

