#### Data extraction and statistical analysis

Data will be described in a database previously built in Microsoft Excel and exported to the Statistical Package for Social Science Version 18.0 software (SPSS Version 20.0), where descriptive and inferential analyses will be performed. The Kolmogorov–Smirnov test will be used to assess the normality of variables. For the evaluation of variables, the Chi-square (χ^2^) or Fisher's Test will also be used. Other tests that may be necessary will also be adopted. Results will be presented through tables, charts and figures, adopting significance level of 5% (*p* = 0.05).

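### The printed sample-size inputs do not give 34 per group for two independent arms; if the Cohen effect of 0.50 is d, power is about 53% two-sided (65% one-sided), not 80%

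*Protocol article*

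**What the plan says.** The Sample size section prints inputs and output together. The calculation, done in G*Power 3.1.9.2, is reported as "with Cohen effect of 0.50, test power of 0.80 and significance level of 5%, establishing N of 34 patients per group"; both arms together make 68. The section does not say which test family was chosen, whether the test was one- or two-sided, or whether the effect is d, f or w.

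The design is stated consistently elsewhere. The abstract describes "68 patients equally allocated into control and experimental groups", Trial design describes a two-arm randomised trial, and Interventions assigns 34 different patients to each arm. Pain on the 0 to 10 VAS is the primary outcome in the abstract. It is also the first item under Primary outcome, which adds vital signs.

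Two further facts bear on the check. Table 1 (Follow-up) marks the VAS once, at F1, 15 minutes after sheath removal, and the Questionnaire section also places it last. Data extraction and statistical analysis repeats the 5% level and names a normality test and the chi-square or Fisher test. It leaves other tests open and names no test for comparing means.

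**The concern.** For a parallel comparison of two means, a standardised difference of 0.50 at 5% and 80% power calls for a little over 60 patients per arm two-sided, or about 50 one-sided. A figure of 34 per arm is far below both. Because the paragraph gives its inputs and its result, the claim can be checked directly and does not depend on a fuller plan.

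The stake is how the result will be read. On the d reading, the trial claims a 20% risk of missing the effect it was sized for, when that risk is nearer 47% two-sided (1 − 0.53) or 35% one-sided (1 − 0.65). The Discussion cites a meta-analysis in which music was not superior to routine care for pain and which asked for new high-quality trials. A null result here would enter that open question with a power statement the design does not support.

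**Working it through.** **Inputs.** From Sample size: effect 0.50, power 0.80, alpha 0.05, 34 per group, 68 in total. From the abstract and Interventions: two independent groups, 1:1. Assumed, because not stated: the effect is Cohen's d; the test is two-sided, with one-sided shown alongside. There is no inflation for dropout, since Data management replaces withdrawals.

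**1. Attempt to reproduce 34 per group with two independent means.**

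Normal approximation: n per group = 2(z₁ + z₂)² / d².

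- Two-sided: 2(1.960 + 0.842)² / 0.25 = 62.8, so 63.
- One-sided: 2(1.645 + 0.842)² / 0.25 = 49.5, so 50.

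Exact noncentral t, with df = 2n − 2 and noncentrality d√(n/2):

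- Two-sided: n = 64 gives power 0.801, so 64 per group, 128 in total.
- One-sided: n = 51 gives power 0.806, so 51 per group, 102 in total.

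A Mann-Whitney test (t-test n divided by a relative efficiency of 0.955 or 0.864) needs 68 to 75 per group two-sided, or 54 to 60 one-sided. The stated figure is not reproduced.

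**2. Power with the stated 34 per group at d = 0.50.**

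Noncentrality = 0.50 × √(34/2) = 2.062, df = 66.

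- Two-sided, critical t = 1.997: power 0.529.
- One-sided, critical t = 1.668: power 0.654.

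**3. Effect detectable with 80% power at 34 per group.**

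Solving the same expression for d gives 0.690 two-sided and 0.609 one-sided. The two-sided value is 0.69/0.50 = 1.38 times the stated effect.

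**4. Calculations in which 34 does appear.**

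| Calculation | Result at 80% power, 5% | Meaning of 34 |
|---|---|---|
| Paired or one-sample t, d = 0.50, two-sided; noncentrality 0.50√34 = 2.915, df 33 | 34 (power 0.808; 33 gives 0.795) | pairs or single subjects |
| One-way ANOVA, two groups, f = 0.50; λ = 0.25 × 34 = 8.5, df 1 and 32 | 34 (power 0.807) | total N, 17 per group |
| Mixed ANOVA interaction, f = 0.25, two measures, correlation 0.5 | 34 | total N |

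For two groups d = 2f, so f = 0.50 is d = 1.0. A chi-square test with w = 0.50 and 1 df needs a total of 32, close to 34 but not equal to it. None of these gives 34 per arm.

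**5. What 68 patients would deliver under other metrics.**

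- f = 0.50 (d = 1.0): power 0.98.
- w = 0.50, chi-square with 1, 2 or 3 df: power 0.98, 0.97 or 0.95.

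**The case against.** The strongest reply is that the paragraph never says d, never says two-sided, and never says the comparison is of means. If 0.50 was Cohen's f, or w for a chi-square test (the only kind of outcome test the analysis section names), 68 patients would have 95% to 98% power and the trial would be more than large enough. This stands as a limit on the conclusion. A reader might infer that the trial's power simply is 53%; the document does not support that without the assumptions of d, a two-sided test and a comparison of means. It does not rescue the paragraph, because under f or w the calculation returns a total of 34 or 32 to 44, so 34 per group is still not its result. A one-sided test does not rescue it either: power is then 65% and 51 per group are needed.

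A reader might also infer that the authors ran a paired test by mistake. The match is exact, but the ANOVA total at f = 0.50 matches equally well and the two explanations exclude each other. The origin of 34 is therefore an inference, and the point does not need it.

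A third reply is that a baseline-adjusted analysis could recover the lost power. Bringing 64 per group down to 34 needs 1 − r² = 34/64, so a baseline correlation r of about 0.69. The protocol gives no such correlation, and Table 1 schedules no baseline VAS to adjust for. The abstract speaks of evaluation at three moments, but the schedule does not place the VAS at the first two. This reply fails on the current schedule.

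**Conclusion.** The point holds in a conditional form. For two independent arms, the stated effect of 0.50, power of 0.80 and 5% level do not yield 34 per group under any independent-groups calculation tried. If the effect is Cohen's d for a comparison of means, 34 per group falls short of the claimed 80% whichever way the test is sided, by about 27 percentage points two-sided and 15 one-sided. The claimed power would need 64 or 51 per group.

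That shortfall depends on the effect being d. That the paragraph is wrong or cannot be reproduced as printed does not: it holds under d, f and w alike. How 34 was obtained remains unknown.

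**What to change.** Rewrite the Sample size paragraph to name the test, its sidedness and the effect metric, and restate the figure so that inputs and output agree for two independent arms.

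- If the metric is d with a two-sided test, say that 34 per group gives about 53% power at d = 0.50 and 80% only at d of about 0.69. Add that a null result will be interpreted by its confidence interval.
- If the metric is f or w, say so, give the total N which that calculation returns, and explain why 68 patients were chosen instead.
- Do not quote power from a baseline-adjusted analysis unless a baseline VAS is added to the schedule.

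The cost is one rewritten paragraph and, on the d reading, a less favourable stated power. No extra patients are required for this. Keeping the claim of 80% at d = 0.50 two-sided would instead need 128 patients, 60 more than the 68 planned.
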